### Randomization

Families will be randomized upon receipt of their signed consent form. Randomization is performed at the family level. In order to keep travelling distances relatively short, randomization is carried out within four strata defined by geographic district in the municipality. We computerize the randomization via an unpredictable random sequence using Java. Critically, this offers allocation concealment. In practice we generate a uniformly distributed random variable on the (0,1) interval. If the assigned value is larger than 0.5, study participants will be offered FSP. If the assigned value is 0.5 or lower, study participants will be offered TAU.

Our aim is to form a new FSP group once at least eight or maximum nine families are assigned to treatment, with the additional aim that the maximum spread in due dates is five weeks. If both aims cannot be fulfilled in practice, the maximum spread in due dates will be prioritized. Hence the group composition will be random. An email with a personal login to the baseline questionnaire is automatically sent upon receipt of the signed consent form. After two automatically generated email reminders (if questionnaires are not filled in) the respondents are notified of their allocation to condition. Respondents who do not fill in questionnaires remain in the study and data are obtained through registers.

In case our restriction on the maximum spread in expected date of confinement causes groups to consist of less than seven families, the group will continue in FSP. However, if this occurs more than four times in a given geographic district during the first three months of project inclusion, we will switch to a block randomization principle within that particular district: once between seven to nine families are assigned to the *study* (keeping the restriction on maximum spread in expected date of confinement) we will create a group and randomization will be carried out at the group level instead.

### Implementation

Randomization and allocation into FSP and TAU will in practice be carried out by use of the program SurveyXact/Results owned by Rambøll Survey; the company that also collects the survey data. Rambøll Survey will code the randomization mechanism, which is concealed to the research team.

### Blinding

The research team and families remain blind to study condition during recruitment, consent and baseline questionnaire, though blinding after this point in time is not possible.

### Statistical methods

Reporting of results will follow the guideline of the CONSORT- statement. Statistical analysis will be intention to treat. The level of significance will be 0.05. The primary endpoint is PSOC at the nine month follow-up. The intention-to-treat analysis will compare FSP with TAU using both simple two-sample t-tests, non-parametric rank based tests (Wilcoxon), and linear regressions (ANCOVA) that control for pre-randomization variables (parents’ age, marital status, educational background, employment status, previous psychiatric/therapeutic treatment, smoking, place of birth, own number of siblings, receipt of welfare, financial strain, and social desirability). This latter analysis will cluster errors at the FSP group level. Except for the divorce rate at the seven year follow-up, which is binary in nature, all statistical analyses of effects on secondary outcomes will follow our strategy for the primary outcome. For divorce rate, we will use simple two-sample t-tests as well as a logistic regression that control for pre-randomization variables. Similar principles will be applied to the analysis of tertiary outcomes.

In addition to intention-to-treat analysis, we will also perform contamination adjusted intention-to-treat analysis, which complements the intention-to-treat approach by producing a better estimate of the benefits and harms of receiving a treatment. This method uses the statistical technique of instrumental variable analysis to address contamination [41-46].

In order to test whether different subpopulations experience differential effects from FSP participation (tertiary outcomes), we will define subpopulations based on pre-randomization variables. The null hypothesis is that subgroups are affected equally by FSP participation. The alternative hypothesis is that subgroups experience differential effects. We will consider mothers with above high school education versus mothers with high school or below; mothers aged 23 or above versus mothers aged below 23; mothers who experienced previous psychiatric/therapeutic treatment versus mothers who did not; families who have experienced financial strain versus families who did not; and families with low relationship stability versus families with high stability. We will, in addition, consider subgroups recruited early (during first six months after study initiation), mid-period (during months 7–12), and late (after month 12). In practice, we will test for significance of subgroup-treatment interactions using t-tests and perform a joint F-test for significance of the entire set of interactions [47].

Because our study collects multiple outcomes, permutation testing methods, and a step-down procedure will be applied to account for the increased likelihood of false discoveries [48]. This is adopted in combination with a naïve evaluation strategy (which examines each outcome individually).

Exploratory analyses that in addition to pre-randomization controls include indicators for the identity of the responsible group leader will be performed to control for variation in program delivery across health visitors. Exploratory analysis will also investigate whether initial group composition affects family outcomes. We will define group composition in terms of the shares of the members of a FSP group that belong to the various subgroups detailed immediately above. Note that group composition by construction will be random conditional on due date and strata.

Finally, as described, we will perform a dropout analysis if more than 1/3 of study participants drop out after initial randomization and prior to the nine months follow-up. In practice we will run a logistic regression of a binary variable indicating dropout as the dependent variable with pre-randomization controls as the independent variables.

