### Secondary study outcomes

*PSOC* measured at 18 months and seven years.

*Parenting stress* is measured with the Parenting Stress Scale [32] at nine months, 18 months and seven years.

*Parenting Quality* is measured at nine and 18 months with the Parenting Scale [33] and we intend to use the HOME inventory as nurse administrative data [34] at nine months. At nine and 18 months, a measure of father-involvement developed for the study and a single item on breastfeeding duration will be included.

*Quality of the Couple Relationship* is measured with the Couple Satisfaction Index [35] during pregnancy at nine months, at 18 months and at six years, and the Coparenting Relationship Scale [36] at nine months and 18 month, and divorce rate at seven years.

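### The covariate list leaves out the pregnancy Couple Satisfaction Index score and the randomization district, which gives up some precision and departs from the stratified design but causes no bias

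*Protocol article*

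**What the plan says.** All references are to the protocol article.

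- **Model.** Statistical methods plans t-tests, Wilcoxon tests and "linear regressions (ANCOVA) that control for pre-randomization variables". The covariates follow in one explicit list of eleven. It opens with age, marital status, education and employment and ends with "previous psychiatric/therapeutic treatment, smoking, place of birth, own number of siblings, receipt of welfare, financial strain, and social desirability". Neither a baseline outcome score nor district is in it.
- **Reach.** With divorce as the sole exception, "all statistical analyses of effects on secondary outcomes will follow our strategy for the primary outcome". Divorce gets a t-test and a logistic regression on pre-randomization variables.
- **CSI.** Under Secondary study outcomes, couple relationship quality "is measured with the Couple Satisfaction Index [35] during pregnancy at nine months, at 18 months and at six years". A comma seems to be missing after the word pregnancy. The data-collection plan lists pregnancy and nine months as separate survey waves, so a pregnancy score is the natural reading.
- **Timing.** Under Randomization, "An email with a personal login to the baseline questionnaire is automatically sent upon receipt of the signed consent form", and allocation is notified only after the reminders. Under Blinding, families and the research team "remain blind to study condition during recruitment, consent and baseline questionnaire".
- **Strata.** Under Randomization, "randomization is carried out within four strata defined by geographic district in the municipality". Each family gets its own uniform draw: "If the assigned value is larger than 0.5, study participants will be offered FSP". A district that yields too many small groups early on may switch to randomizing whole groups.

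**The concern.** An outcome's own baseline score is usually among its best predictors. CSI is the one outcome scale that the protocol says is measured in pregnancy, yet its regression uses a list that fits the primary outcome, PSOC, for which no pregnancy score is listed. Timing does not explain the omission, because financial strain and social desirability are also baseline measures and are on the list. No listed covariate measures couple satisfaction.

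District is known for every family and defines the randomization. The exploratory analysis of group composition itself notes that composition is random only within strata and due date, but the outcome models do not condition on strata.

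At stake are the precision of the CSI effects, which also face a step-down multiplicity procedure, and agreement between design and analysis in every model.

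**Working it through.** **Inputs from the protocol:** d = 0.2 (SD = 1), significance level 0.05 (taken as two-sided), power 0.80, 20% of variance between groups (ICC 0.20), nine families per group, about 230 groups or 2,070 families.

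**Assumed, because the documents give no figure:** pregnancy-to-follow-up CSI correlation r of 0.5 to 0.7; share of CSI variance explained by the listed covariates 10%; share of outcome variance explained by district 0.5-5%. One respondent per family is used throughout.

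**1. The plan's own figure.** Without clustering, n per arm = 2(1.96 + 0.8416)²/0.2² = 392.4, so 393, or 786 in all (the protocol says 800). The design effect is 1 + (9 − 1) × 0.20 = 2.60. Then 786 × 2.60 = 2,044 families, or 228 groups, against the stated 2,070 and 230. The figure reproduces. At 2,070 families the SE is √(4 × 2.60/2,070) = 0.0709 and power is 0.806.

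**2. What pregnancy CSI can explain.** The design effect can be written as 9 × 0.20 + 0.80 = 2.60: a group part of 1.80 and an individual part of 0.80. The score is taken before groups meet, and group composition is random given due date and district. It can therefore explain essentially only the individual part, which falls by r², to 0.80 − 0.25 = 0.55 or 0.80 − 0.49 = 0.31.

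| Clustering | Factor without CSI | r = 0.5 | r = 0.7 |
|---|---|---|---|
| Both arms | 2.60 | 2.35 | 2.11 |
| FSP only (FSP factor + TAU factor) | 2.60 + 1.00 = 3.60 | 2.35 + 0.75 = 3.10 | 2.11 + 0.51 = 2.62 |

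- Both arms: √(2.35/2.60) = 0.951 and √(2.11/2.60) = 0.901, so the SE is 5% to 10% lower. This is worth 1.11 to 1.23 times the families.
- FSP only: √(3.10/3.60) = 0.928 and √(2.62/3.60) = 0.853, so the SE is 7% to 15% lower. This is worth 1.16 to 1.37 times the families.
- Power for d = 0.2 at 2,070 families, both arms clustered: the SE becomes √(4 × 2.35/2,070) = 0.0674 or √(4 × 2.11/2,070) = 0.0639. Power rises from 0.806 to 0.843 or 0.879.

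**3. After the listed covariates.** Suppose they already explain 10% of CSI variance, and the pregnancy score explains that 10% too.

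- Both arms: the starting factor is 2.50. √(2.35/2.50) and √(2.11/2.50) give a further 3% to 8%.
- FSP only: the starting factor is 3.40. √(3.10/3.40) and √(2.62/3.40) give a further 5% to 12%.
- Missing pregnancy scores lower these gains further.

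**4. District, precision.** Let district remove the same share R² from every part of the variance. The SE then falls by 1 − √(1 − R²), which is 0.25% at R² = 0.005 and 2.5% at R² = 0.05. Power moves from 0.806 to 0.808 or 0.825.

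**5. District, validity.** Independent draws at 0.5 were simulated for 2,070 families in four districts (3,000 runs per setting, district effects from none to large, no group effects). Type I error without district was 0.051-0.054, against 0.050-0.054 with it. Omitting district does not distort the test.

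**The case against.** **This is an efficiency choice, not an error.** All three planned analyses are unbiased without these covariates under the stated randomization, the power calculation expressly ignores covariates, and CSI is one secondary scale among several. All of that stands. It limits the weight of the point but does not remove it, since the data are already collected and no reason for leaving them out is given.

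**A separate analysis plan might add the variables.** That cannot be ruled out. But the protocol does not leave the covariates open: it names them and extends the approach to the secondary outcomes. If the wording is loose enough to admit a baseline score, the CSI model is discretionary, and the same sentence is worth writing.

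**Two stronger readings are tempting.** A reader might infer bias from a district's switch to group-level randomization, because the realised FSP share could then differ by district. The documents do not support this: the cut is 0.5 everywhere and no other probability is stated after a switch, so such differences are chance imbalance. Bias would need allocation probabilities that vary by district.

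A reader might also apply √(1 − r²) to the whole SE and expect 13-29%, or 1.3 to 2.0 times the families. That treats families as independent and lets a score taken before the groups form explain the between-group variance that the protocol itself assumes.

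**Conclusion.** The point holds as one of precision and of agreement with the design. The size rests on the assumed r of 0.5 to 0.7 and on the protocol's ICC and group size: 5-10% off the SE of the CSI effect with both arms clustered, 7-15% with only FSP clustered, and less after the listed covariates and missing baselines. With a lower r the gain shrinks and may vanish: at r = 0.3, r² is 0.09, below the 10% credited to the listed covariates in the working. A single range for r is least secure at the last follow-up, years after birth.

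The district gain is small, about 0.25-2.5% in SE for the assumed R². The case for district is mainly that the analysis should follow the stratification, plus some protection against chance imbalance. For PSOC at nine months only this district part applies.

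**What to change.** In Statistical methods:

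- Add the respondent's pregnancy CSI score to every CSI regression. Include a missing-indicator, so that families who did not return the baseline questionnaire, and who by protocol stay in the study, are not dropped. The indicator is acceptable here because baseline response precedes knowledge of allocation.
- Add three district indicators to every ANCOVA and logistic model, including the primary one.
- If a district switches to group-level randomization, add an indicator for that phase, to reduce chance imbalance.

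The cost is wording, fixed before outcomes are seen, and no new data. CSI models use four or five degrees of freedom (score, three districts, missing-indicator) and other models three, with one more for the phase indicator if a switch occurs.

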**Methods/design:**

Participants will be approximately 2500 pregnant women and partners. Inclusion criteria are parental age above 18 and the mother expecting first child. Families are recruited when attending routine pregnancy scans provided as a part of the publicly available prenatal care program at Aarhus University Hospital, Skejby. Families are randomized within four geographically defined strata to one of two conditions a) participation in FSP or b) Treatment As Usual (TAU). FSP aims to prepare new families for their roles as parents and enhance parental access to informal sources of support, i.e. social network and community resources. The program consists of twelve group sessions, with nine families in each group, continuing from pregnancy until the child is 15 months old. TAU is the publicly available pre- and postnatal care available to families in both conditions. Analyses will employ survey data, administrative data from health visitors, and administrative register based data from Statistics Denmark. All data sources will be linked via the unique Danish Civil Registration Register (CPR) identifier. Data will be obtained at four time points, during pregnancy, when the child is nine months, 18 months and seven years. The primary study outcome is measured by the Parenting Sense of Competence scale (PSOC) J Clin Child Psychol 18:167-75, 1989. Other outcomes include parenting and couple relationship quality, utility of primary sector service and child physical health, socio-emotional and cognitive development.

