### Specific objectives and hypotheses

The aims of this study is to determine whether a group-based parent support program can lead to:Early improved parental sense of competence (primary outcome)Continued improvement in parental sense of competence (secondary outcomes)Reduced parental stress (secondary outcomes)Improved quality in early family relationships, that is improved quality of parenting, coparenting and couple relationship quality (secondary outcomes)Improved efficiency in service delivery, that is increasing surveillance of families at risk, and enhancing families’ utility of community resources, social network and family services (tertiary outcomes)Improved child outcomes including better physical health and improved socio-emotional and cognitive development (tertiary outcomes)Heterogeneity of effects across family type with disadvantaged families and families met with a more mature program implementation gaining more from participation (tertiary outcomes).

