### 2.E Sample size

Meta-analytic studies on the effects of parenting education with expectant and new parents found on average small effects on measures of parental adjustment (i.e. PSOC) (*d* = .21, [42]). Stronger effects emerged if interventions included more than five sessions, included an antenatal and postnatal component and were led by professionals rather than semiprofessionals. Thus, we expected *d* = .20 to be a conservative estimate of effect on the primary outcome in the present study.

Findings on our secondary outcomes are more varied depending on the measure used. Parental stress as measured by the Parenting Stress Scale showed effect sizes of *d* = .20 [16] and parenting quality as measured with the HOME inventory (nurse observation, [34]) produced average effect sizes of *d* = .35 SD units [16]. Studies relying on parental self-report found somewhat lower effects; [36], for example, found small effects on coparenting quality (*d* = .18 SD units) and somewhat better effects on parenting quality (ranging from *d* = .30 to *d* = .36), and moderate size effects on relationship satisfaction (*d* = .43). In this study we use both the HOME inventory as well as Feinberg’s measures of parenting and coparenting/relationship satisfaction. Thus we expected *d* = .20 to be a conservative estimate of effects on the secondary outcomes in the present study.

Our primary as well as secondary outcomes all produce interval data that are not cardinal in nature. Thus, the value of a given outcome has no meaning in itself. This is clearly in contrast to many outcomes studied in the medical sciences (e.g. number of days admitted to hospital after surgery). One way of anchoring expected effect sizes is to compare to effects of other interventions. In our case, an effect size of .20 in terms of for example parental stress is comparable to average effects of other types of parenting education [16].

Our power analyses use the 2013 version of the Optimal Design software developed by Spybrook and collaborators. Since treatment in this subproject is carried out at the group-level, we conservatively use the two-level cluster-randomized version with family-level outcomes and ignore the presence of covariates. Assuming that 20% of the variation lies between groups and using a power of 0.80 and significance level of 0.05, we are able to detect an effect size of 0.2 with around 230 groups (115 groups in each condition) or a total of 2,070 families.

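### Secondary outcomes measured at several waves get a single-time-point analysis, so the 18-month and seven-year effects make no use of earlier follow-up scores; one repeated-measures model would use them at small cost

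*Protocol article*

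**What the plan says.** All references are to the protocol article.

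- **Outcomes.** PSOC at nine months is primary. Under Secondary study outcomes, PSOC is also "measured at 18 months and seven years", parenting stress is measured at nine months, 18 months and seven years, and the Parenting Scale and the Coparenting Relationship Scale at nine and 18 months. Specific objectives and hypotheses lists as an aim "Continued improvement in parental sense of competence (secondary outcomes)".
- **Analysis.** Statistical methods names three methods for the primary outcome: a two-sample t-test, a Wilcoxon test, and ANCOVA on a listed set of pre-randomization variables with errors clustered on FSP group. Apart from divorce rate, "all statistical analyses of effects on secondary outcomes will follow our strategy for the primary outcome".
- **Missing data.** Under Randomization, questionnaire non-responders stay in the study through register data. No register source is named for PSOC or parenting stress. The dropout analysis (2.E Sample size and Statistical methods) is run only if more than one third are lost before nine months. It is a logistic regression on pre-randomization variables that describes loss; it does not correct an estimate, and it does not reach loss after nine months.

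**The concern.** A nine-month score is a post-randomization variable, so it is outside the listed ANCOVA covariates. None of the three methods, applied to one wave, takes anything from a parent with no score at that wave. A parent who answers at nine months and is then lost therefore adds nothing to the 18-month or seven-year comparison, although the nine-month score predicts the missing one.

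Two things are at stake. One is precision, which is lost in proportion to the later drop-off and to the square of the between-wave correlation. The other is bias: if the chance of answering later depends on the nine-month score, and does so differently in the two arms, the responders-only contrast is shifted. Such a difference is plausible here. Under Blinding, families know their arm after the baseline questionnaire, and only the FSP arm has continuing group contact, until the child is about 15 months old.

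**Working it through.** **1. The plan's own figure.** Inputs from 2.E Sample size: "using a power of 0.80 and significance level of 0.05, we are able to detect an effect size of 0.2 with around 230 groups", and "Assuming that 20% of the variation lies between groups". Group size is nine families (Abstract: "with nine families in each group"). Allocation is 1:1 (Randomization: "If the assigned value is larger than 0.5, study participants will be offered FSP"). Statistical methods adds: "The level of significance will be 0.05"; I take it as two-sided.

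Groups = 4(1.960 + 0.842)² × [0.20 + 0.80/9] / 0.20² = 4 × 7.849 × 0.2889 / 0.04 = 226.7, or 2,041 families. Noncentral-t power at 230 groups is 80.2%. The stated 230 groups and 2,070 families reproduce. The design effect is 1 + 8 × 0.20 = 2.6.

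**2. Precision at a later wave.** Let f be the share of nine-month responders who also answer later, and r the between-wave correlation. **Both are assumptions.** With two waves and monotone loss, the variance using the nine-month scores, divided by the responders-only variance, is 1 − r²(1 − f).

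| f | r | Cut in variance, r²(1 − f) | Cut in SE |
|---|---|---|---|
| 0.80 | 0.3 | 0.09 × 0.20 = 1.8% | 0.9% |
| 0.80 | 0.6 | 0.36 × 0.20 = 7.2% | 3.7% |
| 0.533 | 0.3 | 0.09 × 0.467 = 4.2% | 2.1% |
| 0.533 | 0.6 | 0.36 × 0.467 = 16.8% | 8.8% |

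The two values of f correspond to 60% and 40% of those randomized answering at the later wave, given 75% at nine months (60/75 and 40/75). The 75% follows from the 25% loss assumed in 2.E Sample size.

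In power for d = 0.20, start from 2,520 × 0.75 = 1,890 families at nine months and apply the design effect of 2.6 to both analyses:

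- f = 0.80: 67.4% on responders only; 68.2% (r = 0.3) to 70.7% (r = 0.6) with the earlier scores.
- f = 0.533: 50.4% on responders only; 52.1% to 57.9% with the earlier scores.

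**3. Bias at a later wave.** Assume standardized bivariate-normal scores and later response that is logistic in the nine-month score. In each arm the responders' mean on the later score is shifted by r times the shift in their mean nine-month score. The bias is the difference between the two arms' shifts.

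| Log-odds slope per SD, by arm | Retention | Absolute bias, r = 0.6 | Absolute bias, r = 0.3 |
|---|---|---|---|
| 0.5 v 0.5 | equal | 0.00 | 0.00 |
| 0 v 0.5 | 69% | 0.09 | 0.04 |
| 0 v 0.5 | 80% | 0.06 | 0.03 |
| 0.25 v 0.5 | 69% | 0.04 | 0.02 |
| 0.25 v 0.5 | 80% | 0.03 | 0.01 |
| 0.5 v 0.5 | 85% v 75% | 0.03 | 0.01 |
| 0.5 v 0.5 | 70% v 50% | 0.06 | 0.03 |

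The sign depends on which arm has the stronger dependence. With a true effect of 0.20, r = 0.6, 80% retention and slopes 0 v 0.5, the responders-only estimate is 0.142 if the slope of 0.5 is in the control arm and 0.259 if it is in the FSP arm. An analysis that conditions on the nine-month score returns 0.20 in both cases.

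**The case against.** The strongest objection is that this is a journal article and the analysis plan is not shown. The article does not write out that later waves use responders only. Imputation that draws on nine-month scores, followed by the named ANCOVA, would be compatible with it. This stands as far as it goes: responders-only analysis is an implication of the named methods, not a statement. But the article does fix a method for these outcomes, and an unseen plan would have to supplement that method to make use of the earlier scores.

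Second, the sizes rest on chosen inputs. This also stands. The 0.09 SD is the largest of the equal-retention cases, the bias vanishes when score-dependent loss is the same in both arms, and the precision gain is small when retention is high or r is low. A low r is quite possible between infancy and age seven. The formula also assumes monotone loss, although skipped waves are possible, and leaves the baseline covariates out. The joint analysis is free of bias here by construction, because loss was made to depend on the nine-month score alone.

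Third, a reader might infer that the aim of continued improvement goes untested. The article does not support that: Secondary study outcomes makes PSOC at 18 months and seven years the measure of it, and Statistical methods tests the arm difference at each. Whether the effect changes between waves is a further question that the article does not pose.

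A reader might also infer that the later effects will be biased, or that loss by seven years is known to exceed 25%. The article gives no retention figure after nine months, so neither can be asserted.

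**Conclusion.** The point holds as a cheap improvement to the analysis of repeatedly measured secondary outcomes, chiefly PSOC and parenting stress at 18 months and seven years. It is not an error or a contradiction in the plan. The named methods leave earlier follow-up scores unused, and nothing else in the article makes up for it.

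The price is a variance larger than it need be: adding the earlier scores would cut it by about 2-7% at 80% retention from nine months and about 4-17% at about 53%, for r between 0.3 and 0.6. Bias is nil under equal score-dependent loss. Under the arm-different patterns it is about 0.03-0.09 SD in most cases, and 0.01-0.02 SD where the contrast between arms is mild and r is 0.3. Against the planning effect of d = 0.20, 0.03-0.09 SD is 15-45%. Retention, correlation and slopes are all assumptions. The nine-month primary analysis, the sample size and the register outcomes are not touched.

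**What to change.** For each scale measured at two or more follow-up waves, estimate the 18-month and, where measured, the seven-year arm effects from one linear repeated-measures model that contains every follow-up wave. Include arm-by-wave effects, the covariates already listed in Statistical methods, an unstructured within-person covariance, and errors clustered on FSP group. Keep the wave-specific ANCOVA as a check. Optionally report the arm-by-wave term as a test of whether the effect persists or fades.

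The cost is a few sentences in the analysis plan and slightly more analysis work; no new data are needed. The model assumes that later scores are missing at random given earlier scores and covariates. That is generally weaker than what the responders-only ANCOVA needs, but it is still an assumption. The joint-model estimates must also be carried into the permutation and step-down procedure for multiple outcomes, and the plan should say how.

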### Setting

This study is conducted in the municipality of Aarhus, Central Region Denmark. The inclusion began on November 24, 2014. Parents will be recruited through Aarhus University Hospital, Skejby, Department of Obstetrics and Gynecology. All pregnant mothers who fulfill the inclusion criteria and are referred from the general practitioner to receive pregnancy care at the hospital will be informed about the study. Information about the study and recruitment will take place at the Ultrasound Department at Aarhus University Hospital in week 12 or 19 of gestational age.

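### FSP group composition is said to be random given due date and district, but time of enrolment also decides which group a family joins

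*Protocol article*

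**What the plan says.** Under Randomization, the Protocol article allocates each family to FSP or TAU, 1:1, within four geographic districts: "Families will be randomized upon receipt of their signed consent form". Group formation comes next: "Our aim is to form a new FSP group once at least eight or maximum nine families are assigned to treatment". A second aim limits how far apart the due dates in one group may lie, to five weeks. Where the two aims conflict, the rule is: "If both aims cannot be fulfilled in practice, the maximum spread in due dates will be prioritized". The section concludes: "Hence the group composition will be random".

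Under Setting, families are approached "in week 12 or 19 of gestational age".

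Under Statistical methods, an exploratory analysis will ask whether a group's initial composition affects family outcomes. Composition is measured by the shares of members in the listed subgroups: education, age, previous psychiatric or therapeutic treatment, financial strain, relationship stability, and recruitment in the early, middle or late period. The stated basis is: "Note that group composition by construction will be random conditional on due date and strata".

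**The concern.** The claim is that, once due date and district are fixed, chance alone decides who sits in a group with whom. The article describes no step that assigns FSP families at random among groups. The only random draw is between FSP and TAU. After that, membership follows from who has been assigned by the time a group is formed.

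Two families in one district with the same due date can enter about seven weeks apart, one at each scan. If the earlier family's group is already full, the two cannot meet. Entry time then determines membership, and it is not in the stated conditioning set.

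What is at stake is how the composition effects are read. If families recruited at week 19 differ from those recruited at week 12, a group's shares partly stand in for the family's own recruitment wave. An apparent effect of group members could then be an effect of the family's own characteristics.

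**Working it through.** The plan gives no figure for group composition, so the check compares the speed of group filling with the gap between the scans.

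**Inputs from the Protocol article.** Sample size: 4,000 births per year, 45% first-born, 80% participation, target 2,520 families. Randomization: 1:1 allocation, four districts, groups of at most nine, five-week limit. Setting: weeks 12 and 19. Dates: November 24, 2014 to at least May 1, 2016 (74.9 weeks). **Assumed:** equal districts, and the split of recruits between the scans, which is not given and is shown as a range.

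**Accrual.** 4,000 × 0.45 × 0.80 = 1,440 families per year. The target then takes 2,520 / 1,440 = 1.75 years, against the article's rough year and a half.

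- FSP families per district-week: 1,440 / 2 / 52 / 4 = 3.46. If all 2,520 arrive in 74.9 weeks: 2,520 / 74.9 / 2 / 4 = 4.2.
- Time to fill a group of nine: 9 / 3.46 = 2.6 weeks, or 9 / 4.2 = 2.1 weeks. If only half of recruits enter at week 12, a group drawn from that wave alone takes 9 / 1.73 = 5.2 weeks.
- Gap between scans for one due date: 19 − 12 = 7 weeks. In that time 7 × 3.46 = 24.2 families enter, enough for 24.2 / 9 = 2.7 groups.

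**Two consequences.**

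1. Families enrolled in the same week at different scans have due dates about seven weeks apart. The five-week limit keeps them out of one group.
2. Families with the same due date enrolled at different scans enter about seven weeks apart. A group usually fills sooner than that, so they seldom share one.

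**Simulation of the rule read as order of entry.** Each family joins an open group if the spread stays within five weeks, and a group has at most nine families. The table gives the percentage of groups with at least seven families that come entirely from one scan.

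| Scenario | 30% at week 19 | 50% at week 19 |
|---|---|---|
| Planned accrual | 93% | 78% |
| Planned accrual, assumed consent lag of 0–4 weeks | about 80% | about 64% |
| Half of planned accrual | about 35% | about 15% |
| Random mixing, groups of nine: p^9 + (1−p)^9 | 4% | 0.4% |

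For groups of seven, random mixing gives 0.7^7 + 0.3^7 = 8% and 2 × 0.5^7 = 1.6%, still well below the simulated values. Half accrual corresponds to 40% participation, the acceptance level below which the article would discontinue the study after six months.

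**Pairs with nearly equal due dates (within 3.5 days) in one district,** with accrual of 3.46 to 4.2 per district-week and groups also closing at week 28. Same-scan pairs share a group with probability 0.61 to 0.78. For different-scan pairs the probability is:

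- 0.002 to 0.015 if 75–90% enter at week 12
- 0.02 to 0.05 if 50% do
- 0.07 to 0.11 if 25% do

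At half accrual the contrast narrows to 0.41–0.57 for different-scan pairs against 0.86–0.91 for same-scan pairs.

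**One share fails without any assumption about how the waves differ.** Recruitment period is itself a composition variable. Near the month-6 and month-12 cut-offs, the scan at which a family enrolled decides its category for a given due date.

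**The case against.** The strongest reply is that little hangs on the sentence. The primary, secondary, instrumental-variable and subgroup-by-treatment analyses do not use group composition. That stands, and it sets the severity.

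Second, sorting is not bias. It matters only if recruitment wave predicts outcomes beyond what the model controls, and the article gives no information on how the two waves differ. Several of a family's own traits are among the planned pre-randomization controls. If these also enter the composition model, which the article does not say explicitly, only unmeasured correlates of wave would remain. This stands too. A reader might infer that the composition effects are confounded, but the document supports only that they may be.

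Third, filling in order of entry is a reading. The article does not say how families are placed when several groups could take them, and a journal article may omit such detail. But no other rule is given, and the article itself derives randomness from the rule it states.

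Fourth, the percentages depend on the assumed scan split, equal districts, planned accrual and prompt consent. This is correct, and the headline figures should not be taken as forecasts. With only 10% recruited at week 19, for example, the variance of the wave share between groups is not inflated. Different-scan pairs with close due dates were nonetheless kept apart more often than same-scan pairs in every pair scenario run.

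Finally, the draw between FSP and TAU does make composition partly random given the order of enrolment. That narrows the fault to an incomplete conditioning set. It does not rescue the claim as worded.

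**Conclusion.** The claim is too strong as written. Under the described procedure, group membership depends on time of enrolment as well as due date and district. At planned accrual a group fills in about 2.6 weeks against a seven-week gap between scans. The sorting is weaker, but still present, at half accrual or with consent delays. These sizes rest on filling in order of entry, equal districts and an assumed scan split.

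The consequence is possible confounding of the exploratory composition effects by a family's own enrolment time, of a size the document does not allow one to state. Two stronger readings should be resisted. A reader might infer that the comparison of FSP with TAU is compromised. It is not, because families are randomized between arms before groups form. A reader might also infer that composition has no random element. It has one, conditional on the order of enrolment. Severity: minor.

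**What to change.** In the exploratory group-composition analysis, condition on enrolment date, or on gestational week at enrolment (week 12 versus week 19), as well as on due date and district. Reword the claim under Statistical methods so that composition is described as random given due date, district and time of enrolment, drop the appeal to construction, and qualify the matching sentence under Randomization in the same way.

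No new data should be needed. Receipt of consent triggers randomization and due date is needed to form groups, so gestational week at enrolment follows from dates the trial must hold. The cost is a small loss of precision in an exploratory analysis, felt most in the recruitment-period shares, which overlap with enrolment date.

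Drawing families into groups by lot after week-19 enrolment has closed would also remove the problem. It would, however, change group formation in a trial already recruiting, and an exploratory analysis does not justify that.
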